## Abstract

**Background:**

Perirenal fat plays a key role in sustaining pathological high blood pressure. We aim to investigate the efficacy of intervention for perirenal fat mediated by focused power ultrasound (FPU) on primary hypertension.

**Methods:**

A multicenter, randomized, sham-controlled, double-blinded trial will be implemented in 200 participants with mild to moderate hypertension. All enrolled participants will be randomly allocated to perirenal fat modification (PFM) intervention using FPU or sham-procedure at a ratio of 1:1 and will be followed up at 24 h, 14 days, 30 days, and 90 days after the intervention. The primary endpoint is changes in office systolic blood pressure (SBP) at 30 days compared with baseline. The secondary endpoints include the changes in office SBP from baseline to 90 days, changes in 24-h mean SBP from baseline to 30 days and 90 days, and changes in heart rate from baseline to 30 days. Safety endpoint is defined as any severe adverse events related to the intervention.

**Discussion:**

The present study is the first to use noninvasive FPU to intervene in perirenal fat to achieve the goal of reducing blood pressure for patients with essential hypertension. Our study is expected to provide a new treatment strategy to control high blood pressure.

**Trial registration:**

ClinicalTrials.gov. NCT05049096. Registered on September 7, 2021.

Protocol version: Version 1.3.1, data 23 August 2021.

Sponsor: [name] is the principal investigator of this trial.

## Introduction

### Background and rationale

Hypertension is one of the most common cardiovascular diseases, whose prevalence exceeds 30% adult population worldwide, and has become the leading cause of global health issues and economic burden [1, 2]. Blood pressure (BP) is deemed to be related to cardiovascular risk. Effective BP management is critical to decreasing the incidence of stroke, heart attack, and heart failure [3–5]. However, the rate of awareness, treatment, and control of hypertension were low, especially in developing countries [5, 6]. The control rate of hypertension in China was even as low as 5.7%, raising great concerns about the health of Chinese individuals [6].

Although pharmacological antihypertensive therapies are the main measures to reduce BP, the percentage of hypertensive patients whose BP attain the target guideline recommendation is unacceptably poor. Exploration of other options to reduce BP is urgent. Visceral fat is closely related to the occurrence of hypertension. Notably, perirenal fat is a unique connected tissue that is well vascularized and innervated [7]. Cumulating evidence showed that perirenal adipose tissue (PRAT) was significantly associated with high BP [7–9] Recently, it was revealed that perirenal adipose afferent nerves played a key role in sustaining pathological high BP in rats [10]. Long-term reduction of BP was observed in spontaneously hypertensive rats by bilateral PRAT ablation [10]. Thus, we hypothesize that the PRAT can be a potential target for lowing BP in clinical practice.

Focused ultrasound is increasingly used in the broad area of medicine, especially in the ablation of solid tissue, such as tumors [11]. This promising treatment could effectively ablate the target area in a non-invasive way with superb precision of energy delivery [12, 13].

Herein, we conducted a multicenter, randomized, sham-controlled, double-blinded study using focused ultrasound to modify the PRAT to explore the efficacy of this kind of modification for the treatment of essential hypertension.

### Objectives

This study is mainly to assess the efficacy of perirenal fat modification (PFM) therapy with focused ultrasound for hypertensive patients with uncontrolled blood pressure. In addition, the occurrence of adverse events (e.g., renal injury, intestinal perforation) will be recorded to assess the safety outcomes.

### Trial design

This is an investigator-initiated, multicentered, randomized, sham-controlled, double-blinded, and exploratory clinical trial with a 3-month duration, which primarily aims to assess whether PFM therapy can reduce blood pressure in patients with grade one to two hypertension.

Eligible participants will be randomized at a ratio of 1:1 into an intervention group and a control group. The participants in the intervention group will receive PFM therapy with focused ultrasound, while a sham procedure will be performed for the participants assigned to the control group. All participants will be assessed for efficacy and safety at 24 h, 2 weeks, 1 month, and 3 months after PFM or sham procedure. The main indicators to evaluate efficacy are the changes in office BP and 24-h ambulatory BP. Adverse events will be recorded at each visit. Blood samples and urine samples will be collected, and imaging examinations will be performed at baseline, 24 h, 1 month, and 3 months. Participants are required to measure their office BP at a 2-week visit. Except for the operator who is responsible for focused ultrasound, all staff, including researchers, statisticians, and participants, are blinded to the groups of randomizations.

This protocol report follows the SPIRIT reporting guidelines [14].

## Methods: participants, intervention, and outcomes

### Study setting

This trial is initiated by the Cardiology Department, The First Affiliated Hospital of Nanjing Medical University. Eligible participants with uncontrolled BP will be recruited at three implementation sites, including the First Affiliated Hospital of Nanjing Medical University (Jiangsu Province), Nanjing Jiangning Hospital (Jiangsu Province), and Suzhou Municipal Hospital (Jiangsu Province).

### Eligibility criteria

The inclusive criteria are as follows:• Individuals aged 18–65 years old• Individuals have uncontrolled BP when receiving a medication regimen of one, two, or three antihypertensive medication classes for at least 4 weeks; and uncontrolled BP is defined as office systolic blood pressure (SBP) ≥ 140 mmHg and < 180 mmHg, and 24-h ambulatory BP monitoring (ABPM) average SBP ≥ 135 mmHg, regardless of diastolic BP• Individuals have at least 20 mm in the anteroposterior, transverse, and axial diameters of inferior perirenal fat measured by ultrasound• Individuals are willing to sign the informed consent of the study

The exclusive criteria are as follows:• Individuals are diagnosed with secondary hypertension (e.g., renal parenchymal hypertension, renal artery stenosis, primary aldosteronism, pheochromocytoma, Cushing’s syndrome, aortic coarctation, severe obstructive sleep apnea-hypopnea syndrome)• Individuals have a history of kidney and or kidney surrounding tissue surgery• Individuals have impairment of liver or kidney function (ALT, AST, or creatinine is greater than 3 times the upper limit of normal reference)• Individuals have a myocardial infarction, unstable angina pectoris, cerebrovascular accident, or transient ischemic attack within 6 months before enrollment• Individuals have type 1 diabetes or poorly-controlled type 2 diabetes• Individuals have uncontrolled thyroid dysfunction• Individuals have urinary calculi and/or hematuria• Individuals have atrial fibrillation• Individuals have severe structural heart disease (e.g., heart valve disease, cardiomyopathy, congenital heart disease)• Individuals have second-degree and above atrioventricular block• Individuals have abnormal coagulation function• Individuals have infected waist skin• Individuals have a malignant tumor• Individuals are pregnant, nursing, or planning to be pregnant• Individuals are unwilling to sign informed consent• Individuals fail to complete the screening period

### Intervention

Eligible patients will undergo either PFM with focused ultrasound or a sham procedure. It is expected that their prescribed antihypertensive medications should be unchanged in the 3 months follow-up period after the intervention.

### PFM procedure

Patients who are assigned to the PFM group will be placed in a lateral position on the treatment bed. Firstly, an ultrasonic probe is used to locate the rough position of inferior perirenal fat and the location needs to be marked on the waist skin. Secondly, a focused power ultrasonic probe is applied to determine the precise target area of perirenal fat. Sequentially, automatic physique measurement starts to calculate the optimal output power for individuals. Lastly, treatment initiates. Bilateral inferior perirenal fat shares the same procedure. The training sessions including recognition of inferior perirenal fat from ultrasonic images and operation of the equipment have been conducted at each study site by only one designated operator.

### Sham procedure

Patients who are assigned to the sham control group share the same procedure as PFM does except that the focused ultrasound will not transmit energy.

### Criteria for discontinuing

Participants may discontinue this trial for any of the following reasons:• They may choose to withdraw for any reason• They have severe side effects that require unmarking to get cured• Their blood pressure is within “escape criteria,” defined as office SBP ≥ 180mmHg or < 90 mmHg• They have a significant deviation from the study algorithm, e.g., changing the established antihypertensive drugs scheme• Any other rational reasons to withdraw from the study

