### Participant timeline

The participant timeline is shown in Table 1. Briefly, all participants will undergo either PFM or sham-control therapy during 14 days screening period. They will be asked to follow up at 1 day, 14 days, 30 days, and 90 days after randomization.

**Table 1 Tab1:** The schedule of enrolment, interventions, and assessments

	Study period					
	Enrolment	Allocation	Post-allocation			Close-out
Timepoint	*− 14 days*	Day 0	*Day 1*	*Day 14*	*Day 30*	*Day 90*
Enrolment:						
Eligibility screen	X					
Informed consent	X					
Interventions:						
* PFM*		X				
* Sham-control*		X				
Assessments:						
Office BP measurement	X		X	X	X	X
24-h ambulatory BP measurement	X		X		X	X
History of diseases	X					
Physical examinations	X				X	X
Drugs use record	X			X	X	X
Antihypertensive drugs concentration tests	X				X	X
Blood routine	X		X		X	X
Biochemical test	X		X		X	X
C-reactive protein	X		X			
Biomarkers of acute renal injury	X		X			
ECG	X		X		X	X
Renal and renal artery ultrasound	X		X		X	X
Carotid ultrasound	X		X		X	X
Cardiac ultrasound	X					
MR imaging of perirenal fat	X				X	X
Functional MR imaging of hypothalamus	X				X	X

*PFM*, perirenal fat modification. *BP*, blood pressure, *ECG*, electrocardiogram *MR*, magnetic resonance

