### Data collection at the final visit

• Office BP and 24-hour ambulatory BP• Anthropometric information including height, weight, waist circumference, and hip circumference• Electrocardiography• Arteries stiffness assessments (PWV)• Imaging examinations including ultrasonic examinations of renal and perirenal fat, carotid ultrasound, and magnetic resonance imaging for perirenal fat and hypothalamic function• Blood tests including routine blood tests, and biochemical blood tests• Urine tests including routine urine tests• Hypertensive drug concentration detection (serum and urine)

All the eligible participants will have comprehensive health examinations and receive PFM therapy or sham-procedure for free. They will have close relationships with physicians who can provide professional consultations and medication guidance for their health problems. Traffic and accommodation subsidies will provide for all participants to promote participant retention and complete follow-up. If participants discontinue follow-up, the reasons will be recorded in detail, and their clinical treatment and other rights shall not be affected.

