### Statistical method

For the primary endpoint, a mixed-effect model for repeated measures (MMRM) adjusted with baseline office SBP will be used to compare the group difference of the office SBP changes from baseline to 1 month. For the secondary endpoint, we will also use the MMRM method adjusted with mean SBP or heart rate to assess the changes in the mean SBP or heart rate from baseline to each visit point. And LS-means method adjusted with baseline SBP or heart rate will be used to estimate the changes in SBP or heart rate and 95% confidence intervals. Imputation for missing values of the main indicator will be conducted using the Markov chain Monte Carlo (MCMC) model which will be performed as the result of the sensitive analysis. We predefine an adverse event of laboratory index that is significantly abnormal at follow-up compared with baseline. Detailed presentation of adverse events will be described and explore the relationship with PFM products. The efficacy analyses will be carried out based on the full analysis set and the pre-protocol set. All baseline characteristics analysis will be conducted on the basis of the full analysis set. The safety evaluation will be analyzed from the safety analysis set. A two-sided *P* < 0.05 will indicate significance in all statistical analyses used by the SAS software V.9.4 (SAS Institute, Cary, NC).

An interim analysis is planned when 50 subjects (100 subjects in total) are enrolled in each group and completed 1 month follow-up, which will be conducted by an independent data monitoring committee (IDMC). The purposes of the interim analysis are as follows: (1) to evaluate the safety (a necessary disruption of the study is considered when there are serious or expected adverse events) and (2) to assess the efficacy. This trial will be expected to terminate in advance if the hypothesis test *P* value is less than the boundary value of the interim analyzed *α* for the primary endpoint. And if the *P* value is greater than interim analyzed *α* with statistical power less than 60%, re-estimating the sample size is needed to make the final statistical power greater than 80%. In accordance with O’Brien-Fleming method, the interim analyzed *α* = 0.005, and final *α* = 0.048.

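### Participants may leave the trial when office SBP meets the escape criteria or antihypertensive drugs change, although the procedure is given once at Day 0, so leaving can only cost outcome data

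*Protocol article*

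**What the plan says.** The section on criteria for discontinuing opens with "Participants may discontinue this trial for any of the following reasons". Two of the listed reasons matter here. One is the escape criteria, "defined as office SBP ≥ 180mmHg or < 90 mmHg". The other is "They have a significant deviation from the study algorithm, e.g., changing the established antihypertensive drugs scheme". The Intervention section sets the matching expectation, "prescribed antihypertensive medications should be unchanged in the 3 months follow-up period after the intervention".

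The Intervention section also says "Eligible patients will undergo either PFM with focused ultrasound or a sham procedure", and Table 1 (Participant timeline) marks that procedure once, in the Day 0 column. On visits, the Participant timeline says "They will be asked to follow up at 1 day, 14 days, 30 days, and 90 days after randomization".

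For those who stop, the section on the final visit says "If participants discontinue follow-up, the reasons will be recorded in detail". The article does not say whether blood pressure is still collected after an escape or a drug change.

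The primary endpoint is the change in office SBP at 1 month (Outcomes). Under Statistical method, the primary analysis is an MMRM adjusted for baseline office SBP, with MCMC imputation as a sensitivity analysis, and "The efficacy analyses will be carried out based on the full analysis set and the pre-protocol set".

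**The concern.** In a drug trial, an escape rule stops study treatment while follow-up can continue. Here no study treatment remains after Day 0, so leaving the trial can only mean that observation ends. The list does not separate the two.

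One exit reason is the primary outcome variable itself, and the other is a usual response to it. Whether a Day 30 or Day 90 reading exists can therefore depend on the blood pressure it would have shown. If PFM works, it can also depend on the arm. Neither the full analysis set nor an SAP can recover a reading that was not taken. At stake are some bias in the Day 30 contrast, more missing data at Day 90, lost safety follow-up in patients of particular interest, and lost precision.

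**Working it through.** **1. Which exits affect which endpoint.** Table 1 schedules office BP at Days 1, 14, 30 and 90. Only exits after Day 1 or Day 14, or between visits before Day 30, cost the primary reading. An escape first seen at Day 30 still supplies it. Exits after Day 30 affect the 90-day endpoints and safety. Entry requires office SBP of at least 140 and below 180 mmHg, so the upper escape limit adjoins the entry range and early escapes are plausible.

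**2. Size of the effect (illustration).** Assumptions not in the documents:
- baseline SBP is normal, truncated to 140–180, with mean parameter 150 or 158 and SD 9;
- correlation between a patient's changes is 0.5–0.7;
- 0%, 25% or 50% of patients with SBP of 160 or more before Day 30 change drugs and leave.

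From the Sample size section: mean falls of 10 mmHg (PFM) and 5 mmHg (sham), SD 13, so the true difference is 5.0. These falls are applied from Day 1.

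| Quantity | Result |
|---|---|
| Leaving before Day 30, escape only | PFM about 1–4%, sham about 2–7% |
| Leaving before Day 30, escape plus drug change | PFM about 4–13%, sham about 7–20% |
| Difference among completers | about 4.3–4.8 mmHg |
| MMRM, exits follow recorded visit readings | 4.97–5.05 mmHg |
| MMRM, drug-change exits follow unrecorded readings | off by about 0.1–0.15 mmHg |

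Relative to 5 mmHg, the completer shortfall is 0.2/5 to 0.7/5, or 4–14%. The MMRM bias with unrecorded triggers is 0.1/5 to 0.15/5, or 2–3%, and its upper part belongs to the heavier drug-change rate. MCMC imputation normally makes the same missing-at-random assumption as the MMRM, so it does not test this.

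**3. Precision.** The plan's own figure first: n = 2(1.960 + 0.842)² × 13²/5² = 106.1, so 107 evaluable per group, and 107/0.85 = 125.9, so 126 with drop-out. The stated 100 is not reproduced at a two-sided 5% level. That is a separate point, but it means there is no spare power.

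Power = Φ(5/(13√(2/n)) − 1.960):
- n = 85 (the planned 15% loss): 5/1.994 − 1.960 = 0.547, power 70.8% (70.3% by noncentral t).
- n = 95: 5/1.886 − 1.960 = 0.691, power 75.5% (75.1% by noncentral t).

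The gain from 85 to 95 is an upper bound. It attributes 10 of the 15 drop-out points to these exits and keeps the difference at 5 mmHg, although patients retained after a drug change may dilute it.

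**The case against.** Several stronger readings are tempting, and the document does not support them.

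- **That participants are compulsorily removed.** The wording is permissive, and the list ends with a general clause for other reasons. What stands is that nothing requires retention, and discretion can vary between sites.
- **That the primary result is biased by 0.5–1.0 mmHg.** One can reach this by assuming 5% exits on PFM, 10–15% on sham, and a Day 30 change 10 mmHg worse in those who leave: (0.05 − 0.10) × 10 = −0.5 and (0.05 − 0.15) × 10 = −1.0. Those rates and that gap are not in the documents, and the sum describes a completer contrast. The plan specifies an MMRM, which uses the Day 1 and Day 14 readings and is close to unbiased when those readings trigger the exit. In the illustration the bias also runs against PFM; it would reverse if exits fell mainly in PFM.
- **That visits definitely stop.** The article is silent, and the full protocol may provide for visits after discontinuation. A separate per-protocol set also makes most sense if deviators' data stay in the full analysis set. This objection has weight. Still, the rule as printed concerns leaving the trial, and the only stated action for those who stop follow-up is to record why.

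Two further points are fair. Table 1 already records drug use at Days 14, 30 and 90 and drug concentrations at Days 30 and 90, so part of the remedy exists. The trial is also labelled exploratory.

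**Conclusion.** The point holds as a weakness in a stated data-collection rule, with a modest effect on the primary analysis. Exit from the trial is tied to the outcome variable or to a response to it, after a one-time procedure, and continued follow-up is not stated. Under the assumptions above, the planned MMRM would be off by nearly nothing when the trigger was recorded at a visit, and by about 0.1–0.15 mmHg when it was not. Completer-type analyses would be off by about 0.2–0.7 mmHg. The loss of precision is at most the step from about 75% to 70% power. Day 90 efficacy and safety data are also exposed, because exits accumulate over a longer period; that loss is not sized here. This should be fixed because it is cheap and because readings not taken cannot be recovered. It does not invalidate the trial.

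**What to change.** Leave the escape limits and all clinical actions unchanged. Amend the section on criteria for discontinuing to state that participants who meet the escape criteria or change antihypertensive drugs stay in follow-up and attend the remaining scheduled visits at Days 14, 30 and 90, unless they withdraw consent. Record the date and type of any drug change. Include all Day 30 readings in the full analysis set for the primary analysis, and add a supplementary analysis that sets readings after a drug change to missing.

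The cost is amendment wording and a small addition to the drug-use record, since the visits are already in Table 1. The downside is that added drugs may dilute the between-arm difference; the supplementary analysis shows by how much. If the full protocol already provides for these visits, it is enough to say so in the article's terms and to state how readings after a drug change enter the primary estimate.

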### Strategies to improve adherence

Before enrollment, we repeatedly confirm the participants’ willingness and compliance with the study’s requirements, especially drug numbers and doses, and being able to follow up within the next 3 months. We make efforts to monitor the adherence to drug use which is prescribed before allocation for at least 4 weeks. Blood and urine samples will be collected to measure the concentration of the antihypertensive drugs (diuretic, calcium channel blocker (CCB), angiotensin-converting enzyme inhibitors (ACEI)/angiotensin receptor blocker (ARB), beta-blocker, and alpha-blocker) at baseline, 1 month, and 3 months.

### Relevant concomitant care and interventions

Though lifestyle modification should be recommended for all hypertensive patients according to the hypertension guidelines, we asked recruited participants to maintain their current lifestyle, including physical activities, diet, and regular rest habits. In order to assess the changes in lifestyle, weight, waist circumference, or hip circumference will be recorded at each follow-up time.

### Outcomes

We speculate that PFM will have a significant blood pressure lowering effects compared with the sham-control group. The endpoints in the present study include primary endpoints, secondary endpoints, and safety endpoints.

Primary endpoint measure:• Changes in office systolic blood pressure at 1-month compared with baseline

Secondary outcome measures:• Changes in office blood pressure at 3 months compared with baseline• Changes in mean systolic blood pressure measured by 24-h ambulatory blood pressure monitoring at 1 month compared with baseline• Changes in mean systolic blood pressure measured by 24-h ambulatory blood pressure monitoring at 3 months compared with baseline• Changes in the heart rate at 1 month compared with baseline• Changes in the mean heart rate measured by 24-h ambulatory blood pressure monitoring at 1 month compared with baseline

Safety endpoint measures:• Any severe adverse events (SAE) related to the intervention. The SAE was defined as acute renal failure, acute intestinal perforation, and thromboembolic events, etc.

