#### Blinding

Study participants and all staff, including investigators, clinical care providers, statisticians, and personnel who recruit, follow-up with participants, and collect data are blinded to the randomizations. The operators will be unblinded to implement the PFM procedure and required to keep blinded to all other staff. After completing the procedure, we will ask about the participants’ feelings or any discomforts and if they can tell the real intervention and sham intervention. Once severe adverse events (SAE) that might be related to the PFM procedure occur, the principal investigators will be able to disclose the arm allocation. The disclosure reason, date, and location will be recorded in detail.

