#### Harms and auditing

In this study, potential risks of PFM therapy are the thermal damage of local skin, subcutaneous tissue, and organs adjacent to perirenal fat. Any discomforts or abnormal indicators changes through energy emission path including skin, muscles, renal area, and intestine will be identified as adverse events (AEs) and will be recorded in eCRF and EDC system with details of onset time, severity, and duration. The severity of AEs and their correlations with PFM therapy will be carefully evaluated in accordance with the Common Terminology Criteria for Adverse Events [17]. Severe adverse events (SAEs) included deaths, life-threatening disease or injury, permanent damage to body structure or function, and diseases requiring hospitalization treatment that are determined by the investigator according to the principles of GCP. Investigators are responsible for dealing with the SAEs to protect the participants as much as possible and reporting the SAEs to the local ethics committee within 24 h. AEs will be reported within 3 days after each visit. All adverse events will be revealed in the trial publication. And the trial will be audited onsite periodically.

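### The safety endpoint uses a different SAE definition from the harms section and counts only SAEs judged related, so unrelated deaths and hospitalisations fall outside it and the comparison with sham rests on attribution

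*Protocol article*

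**What the plan says.** All places are in the protocol article.

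- **Abstract, Methods:** "Safety endpoint is defined as any severe adverse events related to the intervention".
- **Outcomes, safety endpoint:** "Any severe adverse events (SAE) related to the intervention", followed by "The SAE was defined as acute renal failure, acute intestinal perforation, and thromboembolic events, etc".
- **Harms and auditing, SAEs:** "Severe adverse events (SAEs) included deaths, life-threatening disease or injury, permanent damage to body structure or function, and diseases requiring hospitalization treatment". Investigators must report these to the local ethics committee within 24 h. No relatedness condition is attached.
- **Harms and auditing, attribution:** "The severity of AEs and their correlations with PFM therapy will be carefully evaluated in accordance with the Common Terminology Criteria for Adverse Events". The section does not say who judges relatedness, or when.
- **Harms and auditing, adverse events:** "Any discomforts or abnormal indicators changes through energy emission path including skin, muscles, renal area, and intestine will be identified as adverse events". The same section promises that the results publication will show every adverse event.
- **Sham procedure:** identical to the active procedure, but no ultrasound energy is delivered.
- **Concealment mechanism:** site principal investigators are excepted from the bar on viewing allocation, and their authority is limited to urgent unblinding for a serious procedure-related complication.
- **Blinding:** follow-up and data-collection staff are blinded. For SAEs that might be related to the procedure, "the principal investigators will be able to disclose the arm allocation".
- **Statistical method:** safety is analysed in the safety analysis set. Adverse events are described and their relationship to the device is explored.

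**The concern.** One term carries two meanings. In Outcomes an SAE is a short list of complications that a focused-ultrasound procedure might cause, left open at the end. In Harms and auditing it is any event that meets a seriousness criterion, whatever its cause. The endpoint uses the first meaning and adds a relatedness filter.

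Two things are at stake.

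1. **The count.** Two people who apply the article faithfully can reach different numbers of safety endpoint events from the same case files.
2. **The use of the sham arm.** In a randomised, sham-controlled trial, the difference in all SAEs between arms shows whether the procedure adds harm, and nobody has to decide the cause of a single event. An endpoint limited to related events puts individual causal judgements in place of that comparison. A harm that nobody recognises as procedure-related is filtered out, although an excess over sham might have revealed it. Attribution is also sensitive to knowledge of the arm, and the article allows the arm to be disclosed for the very events being judged.

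**Working it through.** No arithmetic decides this point. The article gives no safety event rate, safety hypothesis or safety threshold. The check sets the sections side by side.

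**Step 1. Classify typical events under both texts.**

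| Event | SAE under Harms and auditing? | Counted in the Outcomes endpoint? |
|---|---|---|
| Acute renal failure with hospitalisation, judged related | Yes | Yes |
| Acute renal failure with hospitalisation, judged unrelated | Yes | No |
| Death or other hospitalisation, judged unrelated | Yes | No |
| Death or hospitalisation of a type not listed, judged related | Yes | Undetermined: the list is open-ended |
| Listed complication judged related but meeting no stated seriousness criterion | Not clearly: the criteria are introduced as inclusions, not as a closed set | Yes |

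The texts agree clearly only in the first row. Rows two and three are clear exclusions, and both come from the relatedness filter. Rows four and five are ambiguities, and both come from the two definitions.

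**Step 2. Follow the attribution.** Relatedness is assessed against PFM therapy. A sham participant goes through the same procedure without energy and so has not received that therapy. There are two cases.

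- *Relatedness is recorded while the assessor is blinded.* A sham participant's event can be judged related and counted. The comparison with sham works, although it still omits events judged unrelated.
- *Relatedness is set or revised after the arm is disclosed.* For a participant known to have had sham, a judgement of unrelated is the natural one. Sham events would then tend to leave the endpoint, while events in the PFM arm would face no matching pull. The comparison would be biased, with the sham count too low.

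**Step 3. Ask which case the article secures.** Under Blinding, a possible relation to the procedure is what permits disclosure, so some first suspicion comes before it. No section says that this suspicion is the recorded attribution, that attribution is locked before disclosure, or that it may not be revised. The second case is therefore possible but not prescribed.

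**Step 4. Ask whether all-cause SAEs by arm can still be obtained.** Trial design has adverse events recorded at each visit with no distinction by arm. The safety analysis set is not described as confined to one arm. All adverse events are to be published. The data for an all-cause comparison should therefore exist, but it is not the endpoint that the article specifies.

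**The case against.** The strongest reply is that both definitions are open-ended. The Outcomes list trails off and the harms section speaks of what SAEs included, so one can be read as examples of procedural complications and the other as criteria for expedited reporting. The full protocol, version 1.3.1, is not shown and may hold one definition. This stands in part. It means that a related death is not clearly excluded from the endpoint. It does not remove the relatedness filter, which the Abstract and Outcomes both state, and an open list cannot serve as an endpoint definition.

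Several stronger readings are tempting, and the article does not support them.

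- **That the sham arm cannot serve as a comparator for safety, or that its count is near zero by construction.** Follow-up and data-collection staff are blinded, so a sham event can be judged related. Nothing limits the safety set to the PFM arm, and all adverse events will be published.
- **That unblinded sham events will be called unrelated, or that site staff make the call.** The first is a possibility, not a stated process. For the second, the article does not name who judges relatedness.
- **That adverse events are restricted to the energy path.** The harms section says that changes along that path count as adverse events. It does not say that only those count. Statistical method adds significant laboratory abnormalities, and the SAE texts add deaths, hospitalisations and thromboembolic events. The wording deserves clarification, no more.
- **That a zero-event confidence limit measures the problem.** For no events in 100 participants the one-sided 95% upper limit is 1 − 0.05^(1/100) = 2.95%. That figure is the same under any SAE definition, and the article sets no threshold to compare it with.

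**Conclusion.** The point holds in a limited form. The article defines SAE in two ways that nothing reconciles. It restricts its only safety endpoint to SAEs judged related, so those judged unrelated, including deaths and hospitalisations, fall outside the endpoint. The comparison with sham then depends on a relatedness judgement that disclosure of the arm may influence, and no text requires that judgement to be recorded first. This can weaken or bias the safety comparison but does not disable it.

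The size cannot be expressed as a number, because the article gives no event rate and no proportion of events expected to be judged related.

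The conclusion rests on two assumptions: that the article's sections are applied as worded, and that the safety set includes both arms, which the article implies but does not spell out. If the full protocol already holds a single definition and a rule that attribution is recorded blinded, what remains is a correction to the article and the choice of a related-only endpoint.

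**What to change.** 1. Use the seriousness criteria of Harms and auditing as the single SAE definition, and refer to them from Outcomes.
2. Define the safety endpoint, in Outcomes and in the Abstract, as all SAEs by randomised arm through Day 90, regardless of relatedness.
3. Keep acute renal failure, intestinal perforation and thromboembolic events as a named, closed subset reported separately, and remove the open ending.
4. Report relatedness as a secondary tabulation. State who judges it, and require it to be recorded before any disclosure of the arm.
5. State in Harms and auditing that adverse events are not confined to the energy path.

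A separate wording point should be reconciled at the same time. The interim safety rule in Statistical method reads "a necessary disruption of the study is considered when there are serious or expected adverse events". The article should make clear which events that phrase covers and how it relates to the SAE definition.

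The cost is small: changes to the protocol wording, an eCRF field for the timing of the relatedness judgement, and perhaps slightly more adverse-event entry. The article already provides for adverse events to be recorded at each visit and for SAEs to be reported, so the all-cause endpoint needs no new visits.
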